## Abstract

**Supplementary Information:**

The online version contains supplementary material available at 10.1007/s00702-025-02933-z.

## Introduction

Multiple system atrophy (MSA) is a rare, fatal neurodegenerative disease characterized by progressive autonomic failure, parkinsonian, cerebellar, and pyramidal features in varying combinations (Fanciulli and Wenning 2015). Life expectancy averages less than ten years from symptom onset (Wenning et al. 2013), with common causes of death including urosepsis, aspiration pneumonia, and sudden death during sleep.

Despite existing clinical guidelines for managing key MSA symptoms (Calandra-Buonaura et al. 2021; Brignole et al. 2018; Gibbons et al. 2017; Cortelli et al. 2019; B. Blok 2022; Jordan et al. 2019; Randerath et al. 2017), comprehensive, personalized, multidisciplinary care protocols remain lacking. This poses a challenge for both neurologists and allied health professionals—including psychologists, physiotherapists, speech and occupational therapists—who currently lack regular interdisciplinary collaboration, despite the potential value of concerted pharmacological and non-pharmacological interventions for mitigating MSA symptomatic burden.

Medical tests play a critical role in guiding diagnosis, treatment decisions, and clinical trial enrollment, ultimately affecting patient outcomes. The benefits, risks, and costs of different test-treatment strategies can be systematically evaluated using decision-analytic models (Siebert 2003; Caro et al. 2012), which rely on trial data, registries, literature, and other sources (Siebert 2003). However, no studies to date systematically assessed the benefit-harm balance or cost-effectiveness of MSA test-treatment strategies. Additionally, data on the annual healthcare costs of MSA remain limited (Winter et al. 2011; McCrone et al. 2011), altogether creating a barrier to informed health policy decisions aimed at optimizing care and improving patients’ quality of life (QoL).

Early palliative care has been shown to alleviate the symptoms burden while reducing healthcare costs due to avoidable hospital admissions in chronic neurological conditions, including MSA (Hepgul et al. 2020). Multidisciplinary palliative care programs have been developed in the past for individuals with amyotrophic lateral sclerosis (https://www.hospiz-tirol.at/begleitung/als-netzwerk). However, integration between neurology and specialized palliative care for individuals with MSA services remains limited to date (van Vliet et al. 2016; Oliver et al. 2024; McKenzie et al. 2022).

Beyond the affected individuals, MSA places a significant burden on informal caregivers, i.e., family members or friends who provide unpaid support to those with chronic illnesses (Roth et al. 2015). Caregiver burden encompasses physical, psychological, financial, and social challenges (Zarit et al. 1980), and is influenced by caregiving intensity and supervision hours, with female caregivers often experiencing greater strain (Miyashita et al. 2011; Campese et al. 2024; Shurer et al. 2024; Lindt et al. 2020). Considering that MSA typically results in moderate-to-severe disability within five to six years of onset (Krismer et al. 2024), early familial involvement is essential (Wiblin et al. 2017; Gallop et al. 2023). However, research on the QoL of MSA caregivers remains limited, and support services remain insufficient globally.

The COVID-19 pandemic further exacerbated these challenges by disrupting in-person healthcare services, and increasing the burden on individuals with chronic neurological conditions (Russo et al. 2021; Rakusa et al. 2024). At the same time, the pandemic crisis accelerated the adoption of digital health solutions (Fanciulli et al. 2023). In Parkinson’s disease (PD), telemedicine consultations proved effective for “practicing medicine at a distance” and alleviating the psychological burden of patients and their caregivers (Adams et al. 2020; Fanciulli et al. 2023). Telerehabilitation also demonstrated benefits on parkinsonian motor and non-motor symptoms (Morris et al. 2021; Tamplin et al. 2021; Vellata et al. 2021). For people with MSA, the benefits of remote healthcare may extend beyond the pandemic horizon (Russo et al. 2021), particularly if overcoming physical and geographical barriers enables sustained healthcare delivery at advanced disease stages, when identifying life-threatening complications supports coping (Borders et al. 2021).

Building on the multidisciplinary expertise in MSA care at the Medical University of Innsbruck and its national and international partners, the Medical Decision Making in Multiple System Atrophy (MeDeMSA) Care study has been launched. It aims to evaluate whether a personalized, multidisciplinary care model, integrating mobile palliative care and telemedicine support, can attenuate QoL decline in prospectively recruited individuals with MSA by alleviating the symptomatic burden, ensuring continuity of care, and prioritizing individual healthcare preferences. QoL changes over 18 months are captured with the European QoL Questionnaire – 5 Dimensions – 5 Levels [EQ-5D-5L, (Rabin and de Charro 2001; Feng et al. 2021)] and compared to a matched historical European MSA cohort that received standard care [European MSA Study GroupEMSA-SG, cohort (Wenning et al. 2013)].

Secondary objectives of the MeDeMSA Care study are to assess the acceptance, safety, and cost effectiveness of such an integrated healthcare model, and are detailed in Table 1, along with their respective outcome measures. We here aim at sharing the MeDeMSA Care study design and operational protocols.

**Table 1 Tab1:** Primary and secondary objectives of the MeDeMSA Care Study (left) and respective outcome measures (right)

	Objective	Outcome measure
Quality of life	*Primary*	
	Impact of a multidisciplinary, personalized treatment plan including mobile palliative care (as needed) on the baseline to 18-months change in QoL of prospectively recruited MSA individuals, compared to sex-, age- (± 5 years), and disease duration- (± 12 months) matched MSA individuals from the historical EMSA-SG cohort^a^	- Baseline to 18-months EQ-5D-5L score change
	*Secondary*	
	Impact of a multidisciplinary, personalized treatment plan including mobile palliative care (as needed) on the baseline to 6- and 12-months change in QoL of prospectively recruited MSA individuals, compared to sex-, age- (± 5 years), and disease duration-(± 12 months) matched MSA individuals from the historical EMSA-SG cohort^a^	- Baseline to 6- and 12-months EQ-5D-5L score change - Baseline to 6-, 12- and 18-months changes in the MSA-QoL total score and subscores
Clinical features	Impact of a multidisciplinary, personalized treatment plan including mobile palliative care (as needed) on the baseline to 6-, 12- and 18-months progression of motor, non-motor symptoms and time to clinical milestones of prospectively recruited MSA individuals, compared to sex-, age- (± 5 years), and disease duration- (± 12 months) matched MSA individuals from the historical EMSA-SG cohort^a^	- Baseline to 6-, 12- and 18-months change in motor and non-motor scales (total and subscores, including video-based, rater-blinded assessment of the UMSARS motor subscore and Hoehn & Yahr stage) - Time to clinical milestones (i.e. falls at least once a day, feeding by nasogastric tube or gastrostomy, unintelligible speech, indwelling catheter, wheelchair dependency)
	Baseline to 18-months therapeutic needs of individuals with early versus advanced^b^ MSA	- Medical and neuro-rehabilitation interventional needs over the 18-months study period (see MeDeMSA Operational Protocol in Supplementary Material 1)
	To compare the number of medical complications in individuals with early versus advanced^b^ MSA over the 18-months study period	- Number of medical complications (i.e., falls with or w/o injuries, urinary tract infections, choking, aspiration pneumonia, hospitalizations, death and others) over the 18-months study period
Psychological aspects	To compare the individual healthcare preferences at baseline and after 12 months in individuals with early versus advanced^b^ MSA	- Baseline and 12-months semi-structured online interview - Baseline to 12-months APIS change
	To compare the baseline to 18-months psychological counselling needs in individuals with early versus advanced^b^ MSA	- Psychological counselling needs of individuals with MSA over the 18-months study period (see modular intervention system in the MeDeMSA Operational Protocol, Supplementary Material 1)
	To compare the month 1, 7, 13, and final individual satisfaction with the personalized treatment plan in individuals with early versus advanced^b^ MSA	- Month 1 to 7, 13 and 18 SAPS change referred to the overall individualized treatment plan
Palliative care	To assess the feasibility and barriers to mobile palliative care in individuals with advanced^b^ MSA	- Structured documentation of the palliative intervention - Individual satisfaction with single mobile palliative interventions (IPOS)
HTA	To perform a health technology assessment of an 18-months multidisciplinary, personalized treatment plan including mobile palliative care and telemedicine interventions in individuals with early versus advanced^b^ MSA	- Changes in the EQ-5D-5L, MSA-QoL, motor and non-motor scales, time to clinical milestones, number of medical complications, and satisfaction indices over the 18-months study period - Single-intervention and cumulative healthcare costs over the 18-months study period
Caregivers	To compare the caregiver-burden in informal caregivers of individuals with early versus advanced^b^ MSA over 18-months study period	- Baseline to 6-, 12- and 18-months change in the EQ-5D-5L score of informal caregivers of prospectively recruited MSA individuals - Baseline to 6-, 12- and 18-months change in PQoL Carers score and other caregiver-burden indicators in informal caregivers of prospectively recruited MSA individuals - Baseline and 12-months semi-structured online interview
Telemedicine	To compare the feasibility and barriers to multidisciplinary telemedicine visits in individuals with early versus advanced^b^ MSA	- Individual satisfaction with the single telemedicine interventions, i.e. neurological consultations, psychological counselling, physio-, speech and occupational therapy (online forms, including numeric rating scales and open-end questions) - Healthcare professional’s satisfaction with the single telemedicine consultations (numeric rating scales and open-end questions)
	To assess whether monthly multidisciplinary telemedicine visits in addition to a multidisciplinary, personalized treatment plan including mobile palliative care - Attenuate the baseline to 6-, 12- and 18-months QoL worsening - Attenuate the progression of motor and non-motor MSA symptoms, including time to clinical milestones in prospectively recruited MSA individuals compared to sex-, age- (± 5 years), and disease duration-(± 12 months) matched MSA individuals from the historical EMSA-SG cohort^a^ and to prospectively recruited MSA individuals receiving in-person visits and mobile palliative care (as needed) only	- Baseline to 6- and 12-months EQ-5D-5L score change - Baseline to 6-, 12- and 18-months changes in the MSA-QoL total score and subscores - Baseline to 6-, 12- and 18-months change in motor and non-motor scales (total and subscores, including video-based, rater-blinded assessment of the UMSARS motor subscore and Hoehn & Yahr stage) - Time to clinical milestones (i.e., falls at least once a day, feeding by nasogastric tube or gastrostomy, unintelligible speech, indwelling catheter, wheelchair dependency)
	To assess whether monthly multidisciplinary telemedicine visits in addition to a multidisciplinary, personalized treatment plan including mobile palliative care - Reduce the number of medical complications - Reduce the caregiver burden - Provide an advantage in terms of benefit-harm and cost-effectiveness tradeoffs - Increase the individual satisfaction with the personalized treatment plan over the 18-months study period in prospectively recruited MSA individuals compared to prospectively recruited MSA individuals receiving in-person visits and mobile palliative care (as needed) only	- Number of medical complications (i.e., falls with or w/o injuries, urinary tract infections, choking, aspiration pneumonia, hospitalizations, death and others) over the 18-months study period - Baseline to 6-, 12- and 18-months change in the EQ-5D-5L score of informal caregivers of prospectively recruited MSA individuals - Baseline to 6-, 12- and 18-months change in PQoL Carers score and other caregiver-burden indicators in informal caregivers of prospectively recruited MSA individuals - Baseline and 12-months semi-structured online interview - Single-intervention and cumulative healthcare costs over the 18-months study period - Month 1 to 7, 13 and 18 SAPS change

^a^ In case such matching will not be possible due to unavailable controls from the historical EMSA-SG cohort, a matching between individuals below/above 60 years of age and below/above 3 years of disease duration will be applied

^b^ Advanced MSA: wheel-chair bound at the time of recruitment

*APIS* autonomy preference index survey; *EMSA-SG* European MSA Study Group; *EQ-5D-5L*: European Quality of Life Questionnaire – 5 Dimensions – 5 Levels; *IPOS*: integrated palliative outcome scale; *QoL* quality of life; *MSA-QoL* MSA quality of life questionnaire; *PQoL* carers: carers quality of life questionnaire for Parkinsonism; *SAPS* short assessment of patient satisfaction; *UMSARS* unified multiple system atrophy rating scale *w/o* without

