**Table 2 Tab2:**
[figure not shown]
MeDeMSA Care Patient Visit Plan

During follow-up in-person visits at 6-, 12-, and 18-months, the therapeutic needs are reassessed and the treatment plan is adapted as required. If subjects cannot travel to the center, they are offered the possibility to complete the scheduled on-site assessments via the CHES online platform. At month-12, the semi-structured interview is repeated to evaluate changes in healthcare preferences due to disease progression. Follow-up calls are scheduled one month after each in-person visit (at months 1, 7, and 13) to verify treatment compliance and address barriers. Short Assessment of Patient Satisfaction (SAPS) surveys are administered online at months 1, 7, 13, and 18 to evaluate the overall individual satisfaction with the treatment plan. In case additional in-person visits are scheduled, the reason for such visits and eventual therapeutic adaptations are documented.

Upon completion of the baseline assessment, 23 patients are block-wise randomized to additionally receive monthly and on-demand telemedicine visits for neurological, psychological, and neurorehabilitation support via CHES. If the individuals randomized to receive additional telemedicine visits own a tablet or computer with a ≥ 10-inch display, they may use it to enhance digital comfort. Otherwise, a CE-certified tablet (e.g., SAMSUNG Tab A7 T505 LTE 32 GB) is provided. The MeDeMSA Care team members are asked to rate telemedicine feasibility and potential barriers beforehand. After each telemedicine visit, healthcare providers give feedback on how the visit was conducted, document any challenges encountered, and note the adopted strategies to solve them. Brief patient satisfaction surveys follow telemedicine and mobile palliative care interventions: these include a 0–10 rating scale for the overall satisfaction with the intervention and open-ended questions about its advantages and disadvantages. The MeDeMSA Care team holds regular meetings every six to eight weeks to review changes in the care needs of recruited individuals with MSA and coordinate additional support as required.

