### Data analysis

The distribution of quantitative data will be assessed using the Shapiro–Wilk test. Quantitative variables will be reported as mean (± SD) for normally distributed data or median (interquartile range, IQR) for non-normally distributed data, and qualitative variables as counts (percentages). Qualitative variables will be compared using Pearson’s Χ^2^ test (or Fisher’s exact test, if n < 5) and quantitative variables using the Mann–Whitney U or t-test, depending on the data distribution. A Benjamini–Hochberg correction will be applied for multiple tests, whenever appropriate. Binary logistic regression with a receiver operating characteristics (ROC) area under the curve (AUC) calculation will follow univariate analysis when applicable.

Changes in EQ-5D, motor, and non-motor scores between the MeDeMSA Care cohort and age-, sex-, and disease duration-matched historical EMSA-SG individuals will be evaluated with ANOVA for repeated measurements or linear mixed models, as most appropriate. Comparisons between randomization groups and the historical cohort will be run on a descriptive basis, with post-hoc tests adjusting for type-1 error based on ANOVA results.

QoL and caregiver burden changes in caregivers of MSA individuals receiving personalized best medical care with or without telemedicine will be analysed with ANOVA or linear mixed models, adjusted for the disease stage of the cared-for individual with MSA. Correlation analyses will assess the relationship between the caregivers’ QoL and burden with the disease characteristics (e.g., symptom constellation and severity) of the cared-for individual with MSA.

Statistical analysis will be performed with SPSS version 30.0.0 or future releases. P values below 0.05 will be considered statistically significant, with 95% confidence intervals considered where appropriate.

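### The complication count includes death and ignores follow-up time, and it needs identical event capture in both arms to support the telemedicine comparison

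*Protocol article*

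**What the plan says.** Table 1 uses the same complication outcome for two objectives. Under clinical features the aim is "To compare the number of medical complications in individuals with early versus advanced" MSA; under telemedicine it is to "Reduce the number of medical complications" relative to in-person care. The outcome in both is "Number of medical complications (i.e., falls with or w/o injuries, urinary tract infections, choking, aspiration pneumonia, hospitalizations, death and others", over the 18-month study period.

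The Data analysis section names ANOVA or linear mixed models for EQ-5D, motor and non-motor scores and for caregiver measures. Complications are not named there. What remains for a count is the general rule, "quantitative variables using the Mann–Whitney U or t-test, depending on the data distribution", with "P values below 0.05 will be considered statistically significant". The sample size section expects 10% dropout, and the limitations section names fatal events as one reason for it.

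On contact, Study design says that 23 patients are "block-wise randomized to additionally receive monthly and on-demand telemedicine visits". Both arms share in-person visits at months 6, 12 and 18. In addition, "Follow-up calls are scheduled one month after each in-person visit (at months 1, 7, and 13". The study is open-label.

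Table 1 lists wheelchair dependency among the time-to-event milestones, while its footnote b reads "Advanced MSA: wheel-chair bound at the time of recruitment". Study design states that the historical EMSA-SG cohort was assessed every six months.

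**The concern.** There are two separate problems, and they bear on different comparisons.

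The first is observation time. A patient who dies or leaves early has less time in which to have falls, infections or choking. A raw count reads that shorter exposure as fewer complications. If death is one item in the count, the death puts back one event, which offsets only part of the loss and gives a death the weight of a fall. This matters most for early versus advanced disease, where mortality may well differ.

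The second is ascertainment. Falls and choking often lead to no medical contact, so how many are recorded depends on how often and over what look-back the patient is asked. An arm seen monthly can record more of them at the same true rate. That would work against telemedicine in the very comparison meant to show a reduction.

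Both results go further than a descriptive table. Table 1 lists the number of complications and the time to milestones as inputs to the health technology assessment, and the decision-model section names complications as a harm.

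**Working it through.** The article gives no complication rate, death rate, effect size or power for this outcome, so there is no stated figure to reproduce. The event rates, mortality and capture shares below are assumptions, shown as ranges.

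**Contacts.** Shared scheduled contacts after baseline: 3 visits (months 6, 12, 18) + 3 calls (months 1, 7, 13) = 6. The telemedicine arm adds monthly and on-demand visits.

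**Expected count.** Let r be the non-fatal rate per patient-year, d the 18-month risk of death (constant hazard) and c the share of events captured.

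- Mean follow-up in months: F = 18 × d / (−ln(1 − d))
- Expected count with death as one event: r × c × F/12 + d

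F is 17.55 months at d = 5%, 16.61 at 15%, 16.13 at 20% and 14.09 at 40%.

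**Stage comparison** (c = 1; d = 5% early; r = 2 or 4 per year in early disease).

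Worked case, r = 4, equal true rates, 40% deaths in advanced disease:
- early: 4 × 17.55/12 + 0.05 = 5.90
- advanced: 4 × 14.09/12 + 0.40 = 5.10
- ratio: 5.10/5.90 = 0.86

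| True advanced/early rate ratio | Advanced deaths 20% | Advanced deaths 40% |
|---|---|---|
| 1.0 | 0.95–0.97 | 0.86–0.92 |
| 1.5 | 1.40–1.42 | 1.26–1.32 |

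A simulation of 23 versus 23 patients (gamma–Poisson events with frailty shape 1, 1,500 replicates, two-sided 0.05) gave the same ratios within sampling error. At equal true rates, rejection stayed near 5% (4–7%). With a true ratio of 1.5, t-test power fell from 18–21% when both groups had 5% deaths to 8–13% with 40% deaths in advanced disease. The 23/23 stage split is also an assumption.

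**Arm comparison, truncation only.** With 15% deaths in each arm, equal rates and equal capture, the simulated count ratio was 1.01 and rejection about 5%, so there is no bias. If telemedicine lowered deaths from 25% to 10% at equal rates (r = 4), the counts would be 4 × 17.08/12 + 0.10 = 5.79 against 4 × 15.64/12 + 0.25 = 5.46, a ratio of 1.06. At r = 2 it is 1.03. Better survival would then look like slightly more complications.

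**Arm comparison, unequal capture.** For non-fatal events at equal true rates, the apparent telemedicine/in-person ratio is 1 / (relative capture in the in-person arm):

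- 90% capture: 1/0.90 = 1.11
- 70% capture: 1/0.70 = 1.43

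In the simulation, with death kept in the count, 75% capture gave a ratio of 1.31–1.32 and false rejection of 11–13%. At 90% capture, rejection stayed at about 5%. A true 25% reduction combined with 75% capture in the in-person arm appeared as 0.99, because 0.75/0.75 = 1.

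**Milestones.** Patients in the advanced stratum are wheelchair-bound at recruitment, so they are not at risk for time to wheelchair dependency. EMSA-SG dates rest on six-monthly assessments, so a finer grid in the new cohort would not be comparable.

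**The case against.** The other side has several good points.

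- The Mann–Whitney/t-test sentence is a general rule and is not assigned to complications. The article condenses a fuller protocol, and a rate model may stand there. This is fair: the point is about what the article's own text leads to, and nothing in it brings in person-time.
- Table 1 does not say that event types are summed without weights; tabulation by type also fits. That is possible, but the outcome is worded as one number and death is on the list, so the wording needs to be settled.
- The visit plan (Table 2) is not visible. If complications are captured in both arms by the same diary, look-back or records, the ascertainment problem disappears. This stands, and it makes the second problem conditional.
- Six contacts is a minimum. Both arms may have extra in-person visits and mobile palliative care, and in-person patients who cannot travel may switch follow-ups to telemedicine. Some monthly telemedicine visits may also coincide with the shared schedule. This narrows the contrast but does not remove it.
- Eligibility requires a life expectancy of at least 24 months, which limits early deaths.
- Nothing says that milestones are assessed at monthly telemedicine visits, and some can be dated retrospectively. The six-monthly grid is therefore a safeguard; the wheelchair-bound stratum is a matter of the plan's own definitions.

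A reader might infer that both comparisons are already distorted, or that early death halves the count. The documents do not support either. A death at month 9 halves the exposure of one patient; the group effect computed above is far smaller. Unequal capture is a risk, not a documented fact.

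**Conclusion.** The point holds in a limited form. As written, the outcome mixes death with non-fatal events, and the only stated test that reaches it takes no account of observation time, although deaths and dropout are expected.

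For early versus advanced disease the consequence is attenuation if advanced patients die sooner. It is modest under the mortality assumed here and loses power more than it creates false positives. For the randomized arms, truncation matters only if telemedicine changes survival.

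Unequal capture is potentially the larger effect, with an apparent ratio of 1.11–1.43 when the true ratio is 1.0. It concerns only the arm comparison and rests on an assumed 70–90% relative capture for which the documents give no anchor. Because randomization is stratified by stage, telemedicine contact should not differ systematically between stages.

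The arm comparison is labelled exploratory, the stage comparison is secondary, and the primary EQ-5D result is unaffected. The change is still worth making, because these outcomes feed the health-economic model.

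**What to change.** 1. Report death separately and remove it from the complication count.
2. Analyse non-fatal complications as rates: negative binomial regression with log follow-up time as offset, adjusted for stage in the arm comparison.
3. At the visits common to both arms, elicit events with the same instrument and look-back, whether or not they were already reported by telemedicine, and flag the source of each report. Simply dropping events first reported by telemedicine is not a substitute: an event already handled at a telemedicine visit may not be mentioned again, which would undercount that arm.
4. Use hospitalisations as a sensitivity outcome, since their recording does not depend on how often patients are contacted.
5. For time to wheelchair dependency, exclude patients already wheelchair-bound at entry. For comparison with EMSA-SG, place milestones on the six-monthly grid.

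The cost is slightly more analysis work and one extra field on the event form. With 23 of 46 patients recruited by March 2025, the form change could still cover much of the follow-up; the analysis changes apply to everyone.
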